## 5.5 Data analysis

### 5.5.1 Study power

As this is a pilot and feasibility study, a formal sample size calculation is not required. We aim to recruit at least 40 pwPMS from six centers to assess feasibility across a diverse range of participants including those with different care needs and living conditions. There are no data available on the occurrence of ACP in pwPMS: by hypothesizing a proportion in the pwPMS population of 10%, a sample size of 35 subjects achieves a power of 90%, assuming a type I error of 5%, to detect a proportion of ACP documentation of 30% (Table 2). By hypothesizing a proportion in the pwPMS population of 8%, a sample size of 35 subjects achieves a power of 95%, assuming a type I error of 5%, to detect a proportion of ACP documentation of 30% (Table). By adding 15% of drop outs or incomplete data, 40 pwPMS should be recruited.

**Table 3.** Estimated sample size for one-sample comparison of proportion to hypothesized value.  $H_0$  is the value in the population,  $H_i$  is the alternative value.

| $H_0$ | $H_i$ | Alpha (two-sided) | Power | Estimated required sample size (n) |
|-------|-------|-------------------|-------|------------------------------------|
|-------|-------|-------------------|-------|------------------------------------|

|      |      |      |      |    |
|------|------|------|------|----|
| 0.10 | 0.30 | 0.05 | 0.90 | 35 |
| 0.08 | 0.30 | 0.05 | 0.95 | 35 |

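### Two modest slips in the sample-size paragraph: 40 recruits less 15% leave 34 evaluable rather than 35, and the 90% and 95% power at 35 hold only under a normal approximation.

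*Protocol*

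**What the plan says.** Protocol section 5.5.1 plans a one-sample comparison of the ACP completion proportion with a hypothesised population value, in two scenarios. Both use an alternative of 30% and a 5% error rate.

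- With a null value of 10%, the stated result is "a sample size of 35 subjects achieves a power of 90"%.
- With a null value of 8%, the stated result is "a sample size of 35 subjects achieves a power of 95"%.

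Table 3 repeats both rows under the column "Alpha (two-sided") with the value 0.05. The section then turns 35 into a recruitment target: "By adding 15% of drop outs or incomplete data, 40 pwPMS should be recruited". No exact test is named. The same section says that a pilot needs no formal calculation and sets 40 as a minimum. Section 5.5.2 adds intention-to-treat analysis with multiple imputation.

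**The concern.** The paragraph gives four linked figures: 35 evaluable, 15% loss, 40 recruited, and power of 90% or 95% at two-sided 5%. They should fit together, and they fail to do so in two unrelated ways.

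- **Recruitment target.** Forty recruits do not leave 35 evaluable patients after the stated loss.
- **Power.** The null proportions are so small that only three or four completions are expected under the null with 35 patients. There the binomial distribution is coarse and skewed, and a normal approximation can promise power that no test keeping its 5% error can deliver.

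At stake is whether the power quoted for the primary endpoint can be taken at face value, by readers of the pilot and by whoever checks its assumptions when planning the main trial.

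**Working it through.** **Inputs** (all from section 5.5.1): null p0 = 0.10 or 0.08; alternative p1 = 0.30; two-sided alpha 0.05; power 0.90 or 0.95; required n = 35; loss 15%; recruited 40.

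**1. Reproducing the plan's figures.** The normal-approximation formula is

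n = [(1.960·√(p0(1−p0)) + z_power·√(p1(1−p1))) / (p1−p0)]².

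- Null 10%, power 90%: [(0.588 + 0.587)/0.20]² = 34.5, so 35.
- Null 8%, power 95%: [(0.532 + 0.754)/0.22]² = 34.1, so 35.

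Solved for power at n = 35, the same formula gives 90.3% and 95.4%. Table 3 is therefore correct for this method.

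**2. The inflation.**

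- 40 × 0.85 = 34 evaluable.
- 35 / 0.85 = 41.2, so 42 recruits protect 35.
- 35 × 1.15 = 40.25, which would round up to 41. The stated 40 is this figure rounded down.

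Under the protocol's own formula, 34 evaluable patients give 89.6% and 94.9%. The lost patient costs 0.7 and 0.4 points. If each patient is retained independently with probability 0.85 (an assumption), the chance of at least 35 evaluable is 43% with 40 recruits and 71% with 42.

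**3. Power from the binomial distribution at n = 35.** Expected completions under the null are 35 × 0.10 = 3.5 and 35 × 0.08 = 2.8.

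| Null | Reject at | Upper-tail error | Power at 30% |
|---|---|---|---|
| 10% | ≥7 | 5.5% | 93.5% |
| 10% | ≥8 | 2.0% | 86.7% |
| 8% | ≥6 | 5.7% | 97.3% |
| 8% | ≥7 | 1.9% | 93.5% |

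In each scenario the lower cut-off exceeds 5% in the upper tail alone. The best cut-off that respects 5%, whether one-sided or two-sided, gives 86.7% and 93.5%, so the stated 90% and 95% are not reached.

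The z-test against 10% rejects at ≥7 (z = 1.97) and also at 0 completions (z = −1.97). Its true two-sided error is 5.5% + 0.9^35 = 5.5% + 2.5% = 8.0%.

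**4. The same calculation at 34 and 40**, exact equal-tailed (at most 2.5% in the upper tail):

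| n | Null 10% | Null 8% |
|---|---|---|
| 34 | ≥8: 84.4% | ≥7: 92.1% |
| 35 | ≥8: 86.7% | ≥7: 93.5% |
| 40 | ≥9: 88.9% | ≥8: 94.5% |

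For comparison, the normal approximation at n = 40 gives 93.0% and 97.0%.

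**The case against.** Taking 84% and 92% from the table and setting them against the stated 90% and 95%, a reader might infer that the inflation slip costs about six points and three points of power. The documents do not support this. That comparison mixes an exact calculation at 34 with an approximate one at 35. Like for like, 34 patients still give 89.6% and 94.9%, which round to the stated values. Most of the difference comes from the method.

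The strongest further points on the other side are these.

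- **No exact test is specified.** True, and the choice of test may lie in an analysis plan that is not shown. At n = 34 the result does depend on the rule: the ordinary z-test against 10% rejects at ≥7, with power 92.1% and total error 4.8%, all of it in the upper tail. Against 8% it rejects at ≥6, with power 96.7% and error 5.1%. So 84% is not the only defensible figure at 34. At the protocol's own n = 35 this escape closes, because no upper-tail cut-off with a true error of 5% or less reaches the stated power in either scenario.
- **All 40 may be analysed.** Section 5.5.2 specifies intention to treat with imputation, section 5.3.1 takes the outcome from the medical record, and the completion threshold in section 6 counts recruited patients. This stands as a coherent alternative. The drop-out allowance then has no role, and exact equal-tailed power is 88.9% and 94.5%, slightly below the stated values. Less conservative rules give more.
- **The shortfall is of rounding size.** It is one evaluable patient or two recruits, the target is a minimum, and six centres capped at 12 each allow 72. This stands and limits the severity.
- **Little depends on the test.** Section 5.5.1 disclaims a formal calculation and says that no data support the null value, and section 6 bases progression on fixed thresholds. This also stands. It lowers the urgency but does not make the stated figures right.

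**Conclusion.** The concern holds as two distinct and modest errors.

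- **Inflation:** 40 recruits with 15% loss give 34 evaluable patients, not 35. This costs one patient and under one point of power by the protocol's formula. It rests only on the protocol's own 15%.
- **Power method:** 90% and 95% at 35 are normal-approximation values. With true error held at 5%, they become 86.7% and 93.5%, a loss of about 3 and 1.5 points from the stated figures. This assumes that the nominal 5% in Table 3 is meant as a limit on the actual error.

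The figures quoted for 34 and 40 additionally assume an equal-tailed exact test.

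Severity is low. Table 3 is not miscalculated for the formula it uses, and nothing here shows that the pilot is too small for its feasibility aims.

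**What to change.** Reword section 5.5.1, in one of two ways.

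1. **If the evaluable patients are the denominator:** state that 40 recruits give about 34 evaluable after 15% loss. Label 90% and 95% as normal-approximation values at n = 35. Add the exact equal-tailed two-sided binomial power: 86.7% (null 10%) and 93.5% (null 8%) at 35, and 84.4% and 92.1% at 34. If 35 is to be kept as a firm requirement, the target is 42.
2. **If all recruited patients are the intention-to-treat denominator:** drop the inflation and state exact equal-tailed power of 88.9% (null 10%) and 94.5% (null 8%) at n = 40, for a 30% completion rate among all recruited.

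In both cases, name the test to which the power refers. The cost is a few words and power figures that are somewhat lower. No patients are added unless the sponsor chooses to protect 35, which means two more recruits, well within the existing centre caps.

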### 5.5.2 Statistics

Descriptive statistics will be calculated for general and clinical variables. Specifically, continuous variables will be summarized by their mean and SD, or median and interquartile range; categorical variables will be summarized as numbers and percentages.

Categorical variables will be compared using the chi-squared test. The normality assumption of continuous variables will be tested with the Shapiro-Wilk test. Depending on data distribution, between-group comparisons will be carried out using either the two-sided unpaired t-test or the Wilcoxon two sided two sample test; within-group comparisons will be carried out using either the paired t-test or the Wilcoxon signed-rank test; correlations will be computed using Pearson's or Spearman's coefficients.

Our primary end-point is the proportion of pwPMS completing an ACP during the six-month period. Change in the secondary outcome measures will be also calculated. In addition, we will calculate the following feasibility outcomes:

- Recruitment rate (enrollment per month; reasons for non-eligibility, non-enrollment).
- Retention rate (proportion completing the intervention and study follow-up).
- Missing data (proportion fully completed, for each scale, at each time point).

Data will be analyzed according to the intention-to-treat principle. Multiple imputation of missing values will employ Rubin's approach. A p-value less than 0.05 will be considered statistically significant. No correction for multiple comparisons will be applied. All analyses will be performed using STATA 16 (College Station, Texas 77845 USA). Assumptions in determining the sample size of the main trial will be checked.

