### 3. AIMS

The present study describes the second phase of the *ConCure-SM* project. The objectives of this pilot and feasibility study are as follows:

1. To determine how many people accept the invitation to participate in the study.
2. To determine how many participants receive the intervention.
3. To estimate recruitment and refusal rates, and 6-month follow-up rates.
4. To estimate ACP completion during the 6-month follow-up (primary study outcome).
5. To estimate occurrence of serious adverse events (SAEs) and adverse events (AEs) during the 6-month follow-up.
6. To assess, qualitatively, the acceptability of the recruitment processes, assessments, intervention delivery and secondary outcome measures with key stakeholders.
7. To measure changes in secondary outcome measures.
8. To explore the barriers and facilitators to implementing ACP in pwPMS, and the influence of the clinical setting.
9. To inform the sample size estimation for a subsequent RCT, should this be feasible.

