## 5.2 Pilot study

### 5.2.1 Study design

Multi-center, pilot and feasibility mixed-methods study. It is a non-randomized study (all participants will receive the intervention).

The six centers involved are located in northern (four centers), central and southern Italy (one center each). Two of the centers are rehabilitation hospitals (one of which a research hospital), three are MS centers (two university hospitals, one research hospital) and one is a rehabilitation and MS center from a research hospital.

Recruitment will be competitive, with no pre-specified minimum number of enrolled subjects per center. The maximum number of enrolled subjects per center is 12.

There will be a baseline assessment (T0), an ACP conversation taking place within one month from the baseline assessment, and a follow-up assessment within one week of the ACP conversation (T1) and six months (T2) thereafter. The baseline and follow-up assessments will be performed via the web-based [ConCure-SM](#) platform.

**Table 1.** Summary of trial procedures

|                                         |                                                                                                                                                                                                                                                                                                                                             |                                                                                                                                                                          |
|-----------------------------------------|---------------------------------------------------------------------------------------------------------------------------------------------------------------------------------------------------------------------------------------------------------------------------------------------------------------------------------------------|--------------------------------------------------------------------------------------------------------------------------------------------------------------------------|

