### **5.3.7 Mood symptoms**

*HADS* - The Hospital Anxiety and Depression Scale (HADS) is a self-assessed questionnaire consisting of 14 multiple-choice (0–3 Likert scale) items probing symptoms of anxiety (7 items) and depression (7 items). HADS anxiety (HADS-A) and depression (HADS-D) scores range from 0 (no symptoms) to 21 (most severe symptoms) [Zigmond 1983]. We choose HADS because it is a screening tool with robust psychometric properties, and has been validated in several languages, including Italian [Costantini 1999]. Furthermore, by omitting items assessing somatic symptoms, and thereby limiting false positive findings, the scale is suitable for use in persons with medical conditions [Herrmann 1997]. A cutoff score of 8 or above was recommended for MS patients, since it was found to be an accurate indicator of major depression (90% sensitivity, 87% specificity) and generalized anxiety disorder (88.5% sensitivity; 81% specificity) in this population [Honarmand 2009]. We will use the Italian version of the HADS [Costantini 1999].

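### Chi-squared is the only test named for categorical variables and is not limited to independent groups; applied to the one-proportion primary end-point at n = 35, it would miss the 5% level

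*Protocol*

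**What the plan says.** Protocol section 5.5.2 covers all categorical data in one sentence: "Categorical variables will be compared using the chi-squared test". No exact or paired categorical test is named anywhere in the protocol.

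For continuous data the same paragraph does distinguish the two situations: "between-group comparisons will be carried out using either the two-sided unpaired t-test or the Wilcoxon two sided two sample test", whereas "within-group comparisons will be carried out using either the paired t-test or the Wilcoxon signed-rank test".

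Section 5.2.1 describes the design: "It is a non-randomized study (all participants will receive the intervention". The primary outcome is a single proportion: "Our primary end-point is the proportion of pwPMS completing an ACP during the six-month period". Table 3 in section 5.5.1 carries the title "Estimated sample size for one-sample comparison of proportion to hypothesized value". It gives n = 35 for a null of 10% (power 90%) and for a null of 8% (power 95%), each against 30% at two-sided 5%.

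**The concern.** The test rule does not fit the comparison on which the study was sized. With no control group, the comparison in section 5.5.1 is one observed proportion against a fixed value. A reader who looks in section 5.5.2 for the test of that proportion finds only a large-sample test, and the null values are low enough to make the large-sample approximation poor at this sample size. The actual error rate can then differ from the declared 5%. The power in Table 3 comes from the same approximation, so it describes a test that does not hold its level.

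There is a second, conditional gap. Continuous outcomes have a paired test for change between visits, and categorical ones do not. Anyone who later analyses a category at two visits, for example using the HADS threshold in section 5.3.7 ("A cutoff score of 8 or above was recommended for MS patients"), would be pointed to the wrong test.

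The primary proportion also feeds the decision on a randomized trial and its sample size (sections 3 and 6), so its precision should be stated correctly.

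**Working it through.** **Inputs.** Null 0.10 or 0.08, alternative 0.30, two-sided alpha 0.05, n = 35 (section 5.5.1, Table 3). Recruitment of 40 with 15% loss (section 5.5.1) leaves 40 × 0.85 = 34, so n = 34 and n = 40 are also checked.

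**1. The plan's own figure.** The usual large-sample formula is n = [(z₀.₉₇₅√(p₀q₀) + z_power√(p₁q₁)) / (p₁ − p₀)]².
- Null 0.10, power 90%: [(1.960 × 0.300 + 1.282 × 0.458) / 0.20]² = (1.175 / 0.20)² = 34.5, so 35.
- Null 0.08, power 95%: [(1.960 × 0.271 + 1.645 × 0.458) / 0.22]² = (1.285 / 0.22)² = 34.1, so 35.

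Both entries in Table 3 are reproduced. They rest on the normal approximation.

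**2. Expected counts under the null at n = 35.** 35 × 0.10 = 3.5 and 35 × 0.08 = 2.8, both below 5.

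**3. True size of the one-sample chi-squared test** (no continuity correction; reject when |x/n − p₀| / √(p₀q₀/n) > 1.96; binomial probabilities summed over the rejection region).
- Null 0.10, n = 35: rejects at 0 or at 7 or more completions. P(X = 0) + P(X ≥ 7) = 0.025 + 0.055 = 0.080.
- Null 0.08, n = 35: rejects at 6 or more. P(X ≥ 6) = 0.057.

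| n | Null 10% | Null 8% |
|---|---|---|
| 34 | 4.8% | 5.1% |
| 35 | 8.0% | 5.7% |
| 40 | 5.7% | 3.8% |

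The choice can change a conclusion. With 7 of 35 completions against 10%, z = 0.10 / √(0.09/35) = 1.97 and p = 0.049. The exact binomial p-value is 0.025 + 0.055 = 0.080.

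**4. Exact binomial test at n = 35.**
- Null 0.10: the upper rejection limit is 8 completions. Type I error is 2.0% with a doubled tail, or 4.5% with the version that also rejects at 0. Power at 30% is 86.7%.
- Null 0.08: the limit is 7 completions. Type I error is 1.9% and power at 30% is 93.5%.

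Keeping the stated 90% and 95% with the doubled-tail exact test would take about 45 and 41 evaluable patients.

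**5. Paired categories (illustration only).** Assumptions: n = 35, 30–50% of patients in the category at both visits, within-person correlation 0.3–0.7, no true change, 200,000 simulated samples per setting.
- Chi-squared on the visit-by-visit cross-table rejects in 41% to 99.6% of samples, because it tests association.
- Chi-squared treating the visits as independent groups rejects in 0.05% to 2.0%.
- McNemar's large-sample test rejects in 4.3% to 4.9%.

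For an assumed fall from 50% to 30% with correlation 0.5, power is 35% for the unpaired test and 66% for McNemar's. A worked table shows the contrast. Suppose 12 of 40 patients are in the category at both visits, 20 at neither, and 4 move each way. The prevalence is 16/40 at both visits, yet the association test gives p = 0.0002. McNemar's test gives p = 1.0.

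**6. Independent subgroups.** With splits of 20/20 or 12/28 and a common rate of 10–30%, ordinary chi-squared has a type I error of 3.9% to 5.3%. It is roughly adequate there.

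**The case against.** The sentence has a natural reading on which it is correct. Section 5.5.2 plans between-group comparisons, and one of the aims in section 3 is "To explore the barriers and facilitators to implementing ACP in pwPMS, and the influence of the clinical setting". Chi-squared is a standard test for such independent groups, and step 6 shows that it performs acceptably. A reader might infer from the single-arm design that every comparison here is paired or one-sample, so that the rule is wrong throughout. The documents do not support that.

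A reader might also infer that the protocol plans to compare HADS categories over time by chi-squared. It does not. The threshold appears in the account of the instrument, no analysis uses it, the repeated measures in Table 2 are mainly scale scores, and the eCPS is taken only at T0. The paired figures therefore describe a possible misuse.

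Nor is the primary end-point expressly assigned to chi-squared. The aim is to estimate it, and the progression criterion in section 6 is a point threshold of 25%. The 8.0% is also the largest of the values computed; at n = 34 or 40 the error is close to nominal.

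Finally, naming exact and paired tests is often left to a SAP, which is not shown. That would answer a silent protocol. This one states a rule, separates paired from unpaired tests for continuous data only, and declares alpha and power for a one-sample comparison. The need to qualify the rule and correct the power stands.

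**Conclusion.** The point holds in a limited form. The only categorical rule in section 5.5.2 is too broad for a single-arm study sized on one proportion. If it is used for the primary comparison at n = 35, the two-sided type I error is 8.0% against 10% or 5.7% against 8%, and 3.8% to 5.7% at n = 34 or 40. This needs no assumption beyond the protocol's own inputs and the uncorrected form of the test. With an exact test at n = 35, the power in Table 3 is overstated by about 3 percentage points (86.7% against 90%) and 1.5 points (93.5% against 95%).

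The paired part is conditional on someone comparing categories between visits, and its figures depend on assumed prevalence and correlation. It justifies a clarifying clause, not a claim that planned analyses are invalid. The point is worth correcting but does not threaten a pilot whose main purpose is estimation and feasibility.

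**What to change.** In section 5.5.2, replace the sentence on categorical variables with wording to this effect:
- Independent groups are compared with the chi-squared test, or with Fisher's exact test when any expected count is below 5.
- The primary proportion is reported with an exact binomial 95% confidence interval and, if tested against a fixed value, with an exact binomial test.
- Any binary outcome compared between visits is analysed with McNemar's exact test.

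In section 5.5.1, restate the power at n = 35 as about 87% (null 10%) and 93.5% (null 8%) under the exact test.

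The cost is a few sentences, with no change to data collection or conduct. The one drawback is a slightly less favourable stated power. Should the sponsor wish to keep 90% and 95%, about 45 and 41 evaluable patients would be needed, but a pilot aimed at estimation need not do so.

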### 5.5.3 Qualitative data

Interviews and FGMs will be audio-recorded and transcribed verbatim. Data analysis will be conducted by three researchers with experience in qualitative research.

Researchers will analyze personal interviews and FGM data using thematic analysis, with interpretation guided by NPT components (coherence; cognitive participation; collective action; reflexive monitoring). Data will be triangulated across sources.

The analytical stages can be summarized as follows [Braun 2006]:

- Each researcher will read the transcriptions and write comments and initial thoughts in a memo.
- Each researcher will extract portions of the text individually and then share their work to reach an initial agreement. During this stage, they will conduct the thematic analysis inductively providing their insights.
- Researchers will independently review themes and allocate portions of the text to the newly reconfigured themes.
- Together, they will re-define themes and re-name them to achieve internal consistency.
- One researcher will extract from the interviews and draft the final report, which will be checked and amended by the other two.

